### Secondary outcome analysis

The secondary outcomes of this study are leg pain scores at multiple follow-up time points, functional disability (ODI and RMDQ), mental health assessment (GAD-7 and PHQ-9), and biochemical markers. For leg pain, the NRS scores for leg pain will be analyzed at each follow-up time point using Mixed-Effects Linear Models to account for repeated measurements and intra-patient correlation. This model includes fixed effects for treatment, time, and the interaction between treatment and time. Random intercepts are used to model individual variability over time. Functional disability scores are assessed via changes in ODI and RMDQ measured at 4, 8, and 12 weeks using Mixed-Effects Linear Models. Both measures are treated as continuous variables, and the analysis accounted for repeated measurements within patients. Mental health assessments will be completed using GAD-7 and PHQ-9 anxiety and depression scores, respectively, using Mixed-Effects Linear Models at 4, 8, and 12 weeks. Serum cortisol levels at 4 weeks will be compared between treatment groups using Student’s t-test for normally distributed data, and the Mann–Whitney U test for non-normally distributed data after assessment of normality.

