### Measurement of clinical outcomes

Baseline demographic characteristics, including gender, age, education level, occupation, smoking history, allergy history, family medical history, history of diabetes, and current use of analgesics, will be assessed, in addition to patient measurements such as height, weight, the level of lumbar disc herniation, and the severity of nerve compression measured by Pfirmann grading system base on lumbar MRI (Grade I: Herniated disc in contact with the nerve root without displacement; Grade II: Herniated disc in contact with the nerve root, no nerve root displacement; Grade III: Herniated disc in contact with the nerve root, causing posterior displacement of the nerve root; Grade IV: Herniated disc in contact with the nerve root, compressing it against the posterior wall of the spinal canal) (Majeed et al., 2016). Laboratory parameters, including fasting blood glucose and morning serum cortisol levels will also be measured. Pain intensity will be evaluated using the NRS for both low back pain and leg pain. The Oswestry Disability Index (ODI) and Roland-Morris Disability Questionnaire (RMDQ) will be used to assess functional disability. Generalized Anxiety Disorder 7 (GAD-7) and Patient Health Questionnaire 9 (PHQ-9) were used to assess anxiety and depression.

Follow-up assessments will be conducted at post-injection day 1, week 1, week 2, week 4, week 8, and week 12 (Table 1).

**TABLE 1 T1:** Schedule of enrolment, interventions, and assessments.

Timepoint	Enrolment	Baseline	Allocation	Follow up					
	​	​	0	*Day1*	*Week* *1*	*Week* *2*	*Week* *4*	*Week* *8*	*Week* *12*
Enrolment									
Eligibility screen	X	​	​	​	​	​	​	​	​
Informed consent	X	​	​	​	​	​	​	​	​
Allocation	​	​	X	​	​	​	​	​	​
Interventions									
Dexamethasoe palmitate	​	​	X	​	​	​	​	​	​
Combined betamethasone	​	​	X	​	​	​	​	​	​
Assessmens									
*Pain intensity (NRS score)*	​	X	​	X	X	X	X	X	X
*ODI score*	​	X	​	​	​	​	X	X	X
*RMDQ score*	​	X	​	​	​	​	X	X	X
*PHQ-9*	​	X	​	​	​	​	X	X	X
*GAD-7*	​	X	​	​	​	​	X	X	X
*Serum cortisol* *Levels blood glucose*	​	X	​	​	​	​	X	​	​
*Satisfaction*	​	​	​	​	​	​	X	​	​
*Adverse event*	​	​	​	X	X	X	X	X	X

The primary outcome of this study is leg pain measured by NRS score which is measured on a scale of 0–10, with 0 indicating “no pain” and 10 indicating “the worst pain imaginable” at 4 weeks after procedure.

The secondary outcomes are:

Pain: NRS scores at 1 week, 2 weeks, 8 weeks, and 12 weeks post-injection.

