### Primary outcome analysis

The primary outcome (NRS score at 4 weeks) will be analyzed using a linear mixed-effects model, including treatment group, time, and their interaction as fixed effects, with study center as a random effect, baseline NRS score will be adjusted as a covariate.

Non-inferiority will be assessed based on the between-group difference in mean NRS score at 4 weeks post-treatment, with a pre-specified non-inferiority margin of one point. Non-inferiority will be concluded if the upper bound of the two-sided 95% confidence interval for the between-group difference does not exceed the non-inferiority margin. Both intention-to-treat (ITT) and per-protocol (PP) analyses will be performed to ensure robustness of the results.

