### Subgroup analysis

Prespecified subgroup analyses will be conducted to explore potential effect modifiers, including injection approach (interlaminar vs. transforaminal), herniation severity (Pfirmann grading system based on lumbar MRI), and patient characteristics such as age, sex, and presence of diabetes. Continuous outcomes (NRS, ODI, RMDQ, GAD-7, PHQ-9) will be analyzed using Mixed-Effects Linear Models with fixed effects for treatment, time, subgroup factor, treatment-by-time, and treatment-by-subgroup interactions, and random intercepts for patients to account for repeated measurements.

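### Week-4 cortisol is compared without the baseline cortisol that the trial collects, and the terms listed for the secondary leg-pain model omit the baseline NRS used in the primary model

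*Protocol article*

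**What the plan says.** All places are in the protocol article.

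- **Cortisol.** Under Measurement of clinical outcomes, the baseline paragraph says "Laboratory parameters, including fasting blood glucose and morning serum cortisol levels will also be measured", and Table 1 marks cortisol at baseline and week 4. Under Secondary outcome analysis, "Serum cortisol levels at 4 weeks will be compared between treatment groups using" a t-test if the data look normal and a Mann–Whitney test if they do not.
- **Leg pain.** Under Primary outcome analysis, "The primary outcome (NRS score at 4 weeks) will be analyzed using a linear mixed-effects model", and "baseline NRS score will be adjusted as a covariate". Under Secondary outcome analysis, the leg-pain model is set out as follows: "This model includes fixed effects for treatment, time, and the interaction between treatment and time", with random intercepts. Baseline NRS is not in that list.
- **Questionnaires.** "Functional disability scores are assessed via changes in ODI and RMDQ measured at 4, 8, and 12 weeks using Mixed-Effects Linear Models". GAD-7 and PHQ-9 also get mixed models. No fixed effects or covariates are listed for any of the four scales.
- **Subgroups.** The model has "fixed effects for treatment, time, subgroup factor, treatment-by-time, and treatment-by-subgroup interactions", with random intercepts for patients.

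**The concern.** A baseline measurement of the outcome is often its best single predictor, and the trial already pays for it. The Discussion counts cortisol among the safety outcomes, so a wide interval there weakens one of the comparisons on which any safety advantage would rest. Randomization is stratified by centre, symptom duration and Pfirrmann grade. None of these balances cortisol or NRS directly, so a chance difference at baseline passes into an unadjusted estimate.

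The normality check adds a separate problem. It decides after the data are seen whether the reported result is a difference in means or a comparison of ranks, so the quantity being estimated is not fixed in advance.

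For leg pain, the same scale is given two sets of model terms, with and without baseline, and no reason is offered for the difference. The two models can return different week-4 estimates for one outcome.

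**Working it through.** **Inputs.** From the Study sample size section: SD 2.2, margin 1, true difference 0, one-sided alpha 0.025, power 0.90, 102 per group before dropout and 114 after 10% loss. Assumed, because the document does not give it: baseline-to-follow-up correlation ρ of 0.3, 0.5 or 0.7, with equal variance at both visits.

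**Step 1: the plan's own figure.** n = 2 × 2.2² × (1.960 + 1.282)² / 1² = 101.7, so 102 per group. 102 / 0.9 = 113.3, so 114. Both figures reproduce. Nothing below changes them.

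**Step 2: variance of a single-visit comparison**, relative to the raw follow-up score. Raw = 1; change score = 2(1 − ρ); baseline as covariate = 1 − ρ².

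| ρ | Raw | Change | Adjusted | Sample-size equivalent of adjusting a raw score, 1/(1 − ρ²) |
|---|---|---|---|---|
| 0.3 | 1.00 | 1.40 | 0.91 | 1.10 |
| 0.5 | 1.00 | 1.00 | 0.75 | 1.33 |
| 0.7 | 1.00 | 0.60 | 0.51 | 1.96 |

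**Step 3: cortisol.** With 102 per arm and 80% power, the detectable standardized difference is (1.960 + 0.842) × √[(1 − ρ²) × 2/102]. Unadjusted it is 0.39. Adjusted it is 0.37, 0.34 or 0.28 for ρ of 0.3, 0.5 or 0.7.

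**Step 4: chance imbalance.** One standard error of baseline imbalance is √(2/102) = 0.14 SD. The expected carry-over into an unadjusted week-4 difference is ρ × 0.14 = 0.04, 0.07 or 0.10 SD.

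**Step 5: leg pain at one visit**, if the SD of 2.2 applies. The unadjusted 95% half-width is 1.96 × 2.2 × √(2/102) = 0.60 points. Multiplied by √(1 − ρ²), it becomes 0.58, 0.52 or 0.43.

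**Step 6: ODI and RMDQ.** These are analysed as changes, so the comparison is between the Change and Adjusted columns: 0.91/1.40 = 0.65, 0.75/1.00 = 0.75 and 0.51/0.60 = 0.85. Adding the baseline covariate still helps at every ρ below 1, because the ratio is (1 + ρ)/2.

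**Step 7: the subgroup term.** With no treatment-by-subgroup-by-time term, the treatment-by-subgroup coefficient is the same at every visit. It therefore estimates an average over the modelled visits: six for NRS (day 1 to week 12) and three for the other scales (weeks 4, 8 and 12). A subgroup difference of 1.5 points present only at week 4 has an expected NRS coefficient of 1.5/6 = 0.25. A difference of 1.5 present only at weeks 8 and 12 gives 2 × 1.5/6 = 0.5, although the week-4 value is zero. Those two visits follow a possible second injection, which the Repeat injection section allows to be the alternate study drug.

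**The case against.** **Baseline may already be used.** A reader might infer that the secondary analyses as a whole ignore baseline. The document does not support that. ODI and RMDQ are analysed as changes, which use it. For the four questionnaires no model terms are listed at all: the sentence on fixed effects belongs to the leg-pain model, and a condensed article may leave covariates to an analysis plan that is not shown. The text also does not say whether the baseline visit is one of the modelled time points. If it is, the leg-pain model uses baseline through treatment-by-time. The primary model, if fitted to all visits, would already give baseline-adjusted leg-pain contrasts. All of this stands and limits the firm criticism to cortisol and to the mismatch between the two leg-pain lists.

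**The subgroup model may be deliberate.** A reader might infer that it is wrong because it does not test the week-4 effect. The Subgroup analysis section is exploratory and names no week-4 target. Averaging is also the stronger choice if modification is constant over time. With 204 patients, an even subgroup split, SD 2.2 and within-patient correlation 0.5 (the last and the split being assumptions), the standard errors are about 0.47 for the averaged term and 0.62 for a week-4 contrast. A constant 1.5-point modification then has about 89% power against 68%. If modification occurs at week 4 only, the ranking reverses: 60 simulated trials under the same assumptions rejected 8% with the averaged term and 62% with the week-4 contrast. This is a trade-off and not an error.

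**The size is assumed.** No correlation is in the document, no power is claimed for secondary outcomes, and at 0.3 the gain for a raw score is only 9% of the variance. This is fair, but the gain costs nothing.

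**Conclusion.** The point holds for two stated methods. The week-4 cortisol comparison leaves out a baseline value that the trial collects and picks its test by a normality check. The terms listed for the secondary leg-pain model omit the baseline NRS that the primary model includes. The consequence is lost precision and exposure to chance imbalance, with no bias on average under randomization. For assumed correlations of 0.3 to 0.7, between 9% and 49% of the variance of an unadjusted single-visit comparison could be removed. For ODI, RMDQ, GAD-7 and PHQ-9 the point is a recommendation to state baseline adjustment, since the article lists no covariates for them. The subgroup term needs an accurate description and no more. The primary non-inferiority test, the 102 and 114 per group, and the adverse-event comparisons are untouched.

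**What to change.** 1. Analyse week-4 cortisol by ANCOVA with baseline cortisol as covariate, in place of the test chosen by the normality check. Put both on the log scale if skewed, and settle the scale on pooled, blinded data.
2. Add baseline NRS to the secondary leg-pain model, or state that one baseline-adjusted model supplies the contrasts at every visit.
3. Include each outcome's own baseline as covariate in the ODI, RMDQ, GAD-7 and PHQ-9 models.
4. Optional: describe the treatment-by-subgroup term as an average over the modelled visits, including those after a possible repeat or switched injection, and report a week-4 subgroup contrast for NRS beside it.

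The cost is wording in the analysis sections, best settled before unblinding. All the baseline data are already scheduled, so no extra visits, samples or patients are needed.

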### Subgroup analysis

Prespecified subgroup analyses will be conducted to explore potential effect modifiers, including injection approach (interlaminar vs. transforaminal), herniation severity (Pfirmann grading system based on lumbar MRI), and patient characteristics such as age, sex, and presence of diabetes. Continuous outcomes (NRS, ODI, RMDQ, GAD-7, PHQ-9) will be analyzed using Mixed-Effects Linear Models with fixed effects for treatment, time, subgroup factor, treatment-by-time, and treatment-by-subgroup interactions, and random intercepts for patients to account for repeated measurements.

### Adverse events

The occurrence of adverse events (AEs) will be reported by treatment group. A Chi-square test or Fisher’s exact test (for categorical data) will be used to compare the occurrence of AEs between the two groups.

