**Expected outcomes:**

This study will provide the first high-quality evidence on the efficacy and safety of DEP compared with standard particulate corticosteroids for lumbar radiculopathy. Findings are expected to inform clinical decision-making and optimize steroid selection for epidural therapy.

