## Introduction

Lumbar disc herniation is a common cause of radicular pain and disability in adults, resulting from nerve root compression by displaced disc material (Ropper and Zafonte, 2015; Deyo and Mirza, 2016). Epidural steroid injections (ESIs) are widely used and recommended by the North American Spine Society (NASS) guidelines as a cost-effective option that provides significant pain relief in patients with lumbar radiculopathy (McLain et al., 2005; Liu et al., 2023; Kreiner et al., 2014).

Steroids used in ESIs are categorized as particulate and non-particulate types, and differ in their pharmacokinetics, duration of action, and potential side effect profiles. Particulate steroids, such as triamcinolone and compounded betamethasone preparations, have a larger molecular size and remain at the injection site longer due to their delayed absorption (Benzon et al., 2007), a property that theoretically allows for a prolonged anti-inflammatory effect, and may result in more sustained pain relief (Cole and Schumacher, 2005). However, recent case reports have documented instances of paraplegia in patients following lumbosacral nerve root blocks that utilized the particulate steroids betamethasone or methylprednisolone acetate (Aprill and Melfi, 2004; Houten and Errico, 2002). The use of particulate corticosteroids for epidural injections has also been cautioned against by the FDA in 2011 and 2014, stating that “injections into the epidural space may result in rare but serious adverse events, including loss of vision, stroke, paralysis, and death.” Although particulate steroids are associated with rare but serious complications, including spinal cord infarction, they continue to be used in clinical practice, particularly for interlaminar epidural injections or when a longer-lasting anti-inflammatory effect is clinically desirable.

Compared to particulate steroids, non-particulate types (e.g., dexamethasone) are regarded as a safer option for injection into high-risk areas, such as the epidural space and around blood vessels, as they are unable to induce ischemic events due to their small crystalline structure.

Previous studies comparing particulate and non-particulate steroids have suggested that particulate formulations may provide superior analgesic effects and greater short-term improvement in pain outcomes (Bensler et al., 2017).

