### Study sample size

Assuming there is no difference in the mean NRS score between groups at 4 weeks after treatment, with a standard deviation of 2.2, a two-sided α of 0.05 (equivalent to a one-sided α of 0.025), and a power (1–β) of 0.90, and setting a non-inferiority margin of 1 (less than the minimal clinically important difference of 1.5), a 1:1 allocation ratio between the experimental and control groups was used. Based on PASS software calculations, 102 participants per group were required. After accounting for an estimated 10% loss to follow-up and refusal rate, the final required sample size was determined to be 114 participants per group (Feeley et al., 2017).

A non-inferiority margin of one point on the NRS was selected based on the established minimal clinically important difference (MCID) for radicular pain. This margin was chosen to balance statistical rigor with clinical relevance, allowing detection of whether dexamethasone palmitate maintains acceptable analgesic efficacy compared with standard corticosteroid therapy. From a clinical perspective, demonstrating non-inferiority would support the use of dexamethasone palmitate as a viable alternative treatment option, particularly if it offers additional pharmacological advantages such as prolonged tissue retention or improved safety characteristics.

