Functional disability: ODI and RMDQ at 4 weeks, 8 weeks, and 12 weeks post-injection.

Mental health assessment: GAD-7 and PHQ-9 at 4 weeks, 8 weeks, and 12 weeks post-injection.

Biochemical markers: Morning serum cortisol levels at 4 weeks post-injection. For participants with a pre-existing diagnosis of diabetes, fasting blood glucose will be monitored daily for seven consecutive days post-injection.

Patient satisfaction: Patient satisfaction will be evaluated at 4 weeks post-injection using a structured questionnaire. Satisfaction will be rated on a five-point Likert scale: very dissatisfied, dissatisfied, neutral, satisfied, and very satisfied. In addition, patients will provide a global impression of treatment effect, categorized as: marked improvement, moderate improvement, slight improvement, no change, mild deterioration, moderate deterioration, or severe deterioration.

Throughout the follow-up period, patients will be allowed to continue their pre-existing medication regimens. Concomitant medication use, including nonsteroidal anti-inflammatory drugs (NSAIDs), tricyclic antidepressants (TCAs), and gabapentinoids, will be recorded in detail at each visit, including type, dose, frequency, and duration.

Incidence of adverse events defined as any unintended and harmful outcome that occurs during or after the procedure, which may be directly or indirectly associated with the intervention.

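### The abstract promises comparative safety evidence, but 114 patients per arm and a test of no difference cannot compare the rare serious events behind the safety rationale

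*Protocol article*

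**What the plan says.** - **The promise.** Abstract, Expected outcomes: "This study will provide the first high-quality evidence on the efficacy and safety of DEP compared with standard particulate corticosteroids for lumbar radiculopathy". The sentence carries no qualification.
- **The safety concern.** Introduction: "Although particulate steroids are associated with rare but serious complications, including spinal cord infarction". The same paragraph cites a regulator's warning about stroke, paralysis, visual loss and death after epidural injection.
- **The sample size.** Study sample size bases 114 per group on the week-4 pain score only. It adds that non-inferiority would support use of dexamethasone palmitate (DEP), "particularly if it offers additional pharmacological advantages such as prolonged tissue retention or improved safety characteristics". No AE rate, safety margin or power for AEs is given.
- **The AE outcome.** Measurement of clinical outcomes sets a broad definition: "Incidence of adverse events defined as any unintended and harmful outcome that occurs during or after the procedure".
- **The AE analysis.** Adverse events: "The occurrence of adverse events (AEs) will be reported by treatment group", followed by "A Chi-square test or Fisher’s exact test (for categorical data) will be used to compare the occurrence of AEs between the two groups". No other between-arm method for AEs is stated.

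**The concern.** If non-inferiority on pain is shown, the reason to prefer DEP must come from its other properties. Safety is a main one that the article offers. The events that make safety an issue are rare and severe, while the sample size was chosen for a continuous pain score.

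A test of no difference also does not address whether one drug is as safe as the other. For pain, the plan uses a margin and a confidence interval, so an imprecise result cannot pass as a favourable one. For AEs it states neither. A non-significant result is likely for uncommon events whether or not the drugs differ, and a p-value alone does not show how large a difference remains possible. The abstract's sentence could then be taken as fulfilled when the data say very little about the events in question.

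**Working it through.** **Inputs from the article.** SD 2.2, margin 1, true difference 0, one-sided α 0.025, power 0.90, 10% loss, 114 per arm enrolled and 102 evaluable (Study sample size). The AE rates below are assumptions.

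**1. The plan's own figure.** n per arm = 2 × SD² × (1.960 + 1.282)² / margin² = 2 × 4.84 × 10.51 / 1 = 101.7, so 102. With loss: 102 / 0.90 = 113.3, so 114. Both stated numbers reproduce. The size is right for pain; the article makes no such calculation for AEs.

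**2. No events in an arm.** The exact one-sided 95% upper bound is 1 − 0.05^(1/n).
- n = 114: 1 − 0.05^(1/114) = 2.6%.
- n = 102: 1 − 0.05^(1/102) = 2.9%.

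**3. Chance of seeing even one event in an arm of 114**, 1 − (1 − p)^114:
- p = 0.1%: 11%
- p = 0.5%: 44%
- p = 1%: 68%

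**4. Smallest split that reaches significance against zero events**, Fisher's exact test, 114 per arm:
- 5 versus 0: p = 0.060
- 6 versus 0: p = 0.029

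The expected count at 5 versus 0 is 2.5 per arm, so Fisher's test and not chi-square would ordinarily apply.

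**5. Power at 114 per arm**, two-sided 0.05, by enumerating all pairs of binomial outcomes:

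| Assumed AE rates | Fisher | Chi-square |
|---|---|---|
| 2% vs 1% | 1% | 7% |
| 5% vs 2.5% | 8% | 15% |
| 10% vs 5% | 22% | 31% |
| 20% vs 10% | 50% | 57% |
| 30% vs 15% | 74% | 78% |
| 25% vs 10% | 82% | 86% |
| 40% vs 20% | 89% | 92% |

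For 80% power by the usual chi-square formula, a halving needs about 2,319 per arm from 2%, 435 from 10%, 199 from 20% and 121 from 30%.

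**6. What an interval would show.** With equal true rates, the approximate 95% half-width for the risk difference is 1.96 × √(2p(1 − p)/114):
- p = 5%: 5.7 percentage points
- p = 10%: 7.8 points
- p = 20%: 10.4 points

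At a 10% rate in both arms, a typical result would still allow a true difference of nearly 8 points either way. A p-value would not reveal this.

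**The case against.** Sizing a trial on its primary efficacy outcome is ordinary, and chi-square or Fisher is a conventional comparison of AEs. An article may also leave interval methods and AE categories to an analysis plan. All of this stands: the test is not an error, and missing detail is not the point. The point is that the article itself fixes both the claim and the one comparison meant to support it, and the two do not match.

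Four stronger readings are tempting, and the article does not support them.

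- **That the trial cannot show any safety difference.** The AE definition is broad enough to count common minor events, and large differences in these are detectable: 25% versus 10% has 82–86% power, and 40% versus 20% has 89–92%.
- **That the investigators will read non-significance as safety.** No section sets such a rule. It is a foreseeable misreading that the text does not guard against, and the limitations in the Discussion do not mention it.
- **That the 1-point margin was accepted in exchange for safety gains.** Study sample size bases the margin on the minimal clinically important difference. Safety comes afterwards and conditionally.
- **That the whole article over-promises.** The last paragraph of the Introduction speaks only of potential advantages, and the Conclusion says only that the study may provide relevant data. The sentence in the abstract is the unqualified one.

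The plan also goes beyond a bare p-value. AEs are to be reported by arm, and Data and safety monitoring provides for severity, causality, duration and serious events.

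**Conclusion.** The concern holds as a mismatch between a stated claim and a stated method. At 114 per arm the trial cannot compare the rare serious events described in the Introduction: zero events leaves rates up to 2.6% open, and 5 versus 0 would not be significant by Fisher's test. For common AEs its ability depends on the rate. Power for a halving is 22–31% from 10%, 50–57% from 20% and 74–78% from 30%. A non-significant test would not show equal safety.

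The zero-event bound and the Fisher p-values depend only on the arm size. The power figures rest on assumed AE rates and on all 114 per arm being assessed; with 102 they are somewhat lower. The primary pain analysis and its sample size are not affected.

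**What to change.** 1. **Adverse events.** Make the risk difference with a 95% confidence interval (score or exact) the main between-arm comparison for any AE, procedure-related AE and serious AE. Keep any p-value as secondary.
2. **Same section.** Where no serious neurological or vascular event is seen, report the exact upper bound on its rate. State that a non-significant difference is not evidence of equal safety.
3. **Abstract, Expected outcomes.** Limit the safety claim to common short-term AEs.
4. **Discussion, limitations.** Add that the trial is too small to compare rare serious events between the two drugs.

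The Conclusion is already hedged and needs no change.

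The cost is wording in three places and a different summary of data already collected, with no added patients or visits. The downside is a more modest safety claim.
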